### Design

We will pilot test the feasibility and acceptability of the intervention in a small RCT among 200 Latino/a MSM and TGW from Bienestar Human Services, Inc.’s (*Bienestar*) HIV testing sites. There will be approximately 90 MSM and 10 TGW in each arm. Participants will complete a survey at baseline, six, and 12 months. Participants will be randomized (procedures for this are described in detail below) into either the “information only” group (e.g. receiving text messages with HIV prevention information) or the “information plus” group (e.g. additionally receiving quiz questions that provide the possibility of winning prizes when answered correctly). Randomization will provide the comparison needed to identify the potential effect of winning a prize.

We will pilot the recruitment process with five participants. We will begin with a staggered enrollment process based on previous HIV testing data to identify the highest volume *Bienestar* sites. During the study we are collecting quantitative data on both primary outcomes (e.g. HIV knowledge and frequency of testing behavior) and secondary outcomes (e.g. HIV status).

All participating institutions received approval from their respective Institutional Review Boards and a certificate of confidentiality has been obtained from the National Institute of Mental Health. Any protocol modifications will be submitted to the IRBs for review, and participants will be informed if warranted. The trial was registered on 5 May 2017 with the ClinicalTrials.gov registry (NCT03144336).

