At enrollment, we will take several steps to ensure the confidentiality of participants related to text message communication. For example, as mentioned above, MOTIVES HIV testers will instruct participants how to properly use the SMS system, maintain privacy on their device, and delete SMS messages from their mobile device. Finally, study staff will call the participant (either using an office line or using the *67 feature to make a protected call using their personal cell phone) to confirm that study staff has the correct cell phone contact number for the participant. At this time, participants will receive a $15 gift card.

After participating in the baseline survey and receiving their gift card, participants will be randomized using computer allocation by the study PI. The goal is to ensure that the randomization process does not influence responses to the baseline survey (e.g. responding more quickly if they were not chosen for the prize drawing group and feeling disappointed and less invested in the study). The study design was guided by its purpose as a pilot trial; we used a 1:1 randomization as it provides the greatest power for testing effectiveness in preparation for a future definitive RCT. Hereafter we will refer to the two groups as: (1) Information plus group (intervention group); and (2) Information only group (control group). HIV testers will also reaffirm that assignment is completely random and not based on the personal characteristics of any individual client. RAND study staff will explain to testers why randomization is so important, underscoring that only with their help can we actually understand if the intervention works. If testers select participants based on their own judgment of who is most in need of the intervention (e.g. they think a client appears particularly poor and would really appreciate having gift cards), we would not be able to collect accurate data. If a certain type of client is consistently included in the information plus reminders group, we will not be able to determine if the intervention works with everyone or just with a particular type of person.

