We will conduct group comparisons at six-month intervals to assess the intervention’s short- and mid-term effects. In addition to simple group comparisons at each time point, we will exploit the longitudinal nature of the data by using repeated-measures and time-series techniques. This approach will allow us to examine whether self-reported sexual behaviors persist or decline similarly between the two groups. Repeated measures models will be fitted using Xtreg in the software package Stata. We will use an Analysis of Covariance (ANCOVA) framework to test for group differences, controlling for relevant client characteristics that are found to differentiate the groups at baseline in order to improve the precision that would result from a simple Analysis of Variance (ANOVA) on randomly assigned individuals. For analyses with the dichotomous variables such as HIV testing within a three-months period, we will use a non-parametric McNemar’s test and an analogous multiple logistic regression to control for covariates to assess group differences.

As with any randomized trial (that eliminates selection bias), the first and most direct way to evaluate the impact of an intervention is a simple comparison *D* of the group means in adherence levels.$$ D=E\left[{Y}_i^T\left|T\right.\right]-E\left[{Y}_i^C\left|C\right.\right] $$, *E[Y]* indicates the expected outcome in intervention group *T* and control group *C*.Taking into account the longitudinal nature of the data, this can be written as: $$ D=E\left[\Delta {Y}_i^T\left|T\right.\right]-E\left[\Delta {Y}_i^C\left|C\right.\right] $$In small samples efficiency can be improved by controlling for differences in control variables between the groups that may arise due to chance as discussed above. The approach can be implemented in a regression framework (and again, can be implemented in differences rather than levels): *Y*_*i*_ = *α* + *βT* + *δX*_*i*_ + *ε*_*i*_

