As summarized in Table 1, we will explore a range of variables. The independent variables include control variables not only to improve efficiency, but also to learn about the paths through which the intervention works and to identify subgroups that are likely to particularly benefit from the intervention. Furthermore, potential mediators of behavior, such as level of acculturation, may result in improved provider communication and hence information access. For example, some people may want to avoid being seen at a clinic or HIV testing site, but for people who can communicate with providers more easily, this cost is close to zero, and their behavior may not be altered through the intervention. We can test this effect by forming an interaction between the acculturation measure and the intervention. With respect to the dependent variables, the primary outcomes include HIV knowledge and frequency of HIV testing; the secondary outcomes include HIV infection. Continuous variables will be assessed for normality and transformed if needed. Analyses will be conducted for the whole sample as well as for Latino/a MSM and TGW separately to arrive at the potentially differential impact of the MOTIVES intervention for these two groups. Logit estimation will be used for binary outcome measures.

We will impute missing data for some variables if an individual is still enrolled. When participants drop out, we will fit multiple logistic regression models to assess whether this dropout is random. If it is not, we will construct “non-response” weights using logistic regression that correct for dropout. Analyses will reflect these design effects in the calculation of standard errors and tests of significance.

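### McNemar's test, a test for paired data, is named for comparing HIV testing between two unmatched randomised arms; the fault is confined to that component and should be corrected

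*Protocol article*

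**What the plan says.** The Data analysis section of the protocol article introduces the method with "For analyses with the dichotomous variables such as HIV testing within a three-months period" and continues "we will use a non-parametric McNemar’s test and an analogous multiple logistic regression to control for covariates to assess group differences". The stated purpose is therefore the comparison between arms.

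The arms are described as independent individuals. The MOTIVES intervention section says "participants will be randomized using computer allocation by the study PI" and "we used a 1:1 randomization as it provides the greatest power for testing effectiveness". The Design section says "There will be approximately 90 MSM and 10 TGW in each arm". The Data analysis section itself refers to a "simple Analysis of Variance (ANOVA) on randomly assigned individuals". Matched pairs are not mentioned anywhere.

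The same section defines the effect as D, the expected outcome in the intervention group minus that in the control group, and says that "the first and most direct way to evaluate the impact of an intervention is a simple comparison" of group means. Further on it adds "Logit estimation will be used for binary outcome measures".

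**The concern.** McNemar's test compares two proportions measured on the same or matched people and uses only the discordant pairs. With two separate groups there are no pairs, so the named test has no defined input. An analyst who follows the sentence must improvise one, and different improvisations answer different questions.

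HIV testing is one of the two primary health outcomes, and the Data analysis section gives the three-month yes/no form as an example of what this sentence covers. The logistic regression in that sentence is the covariate-controlled version, which leaves McNemar as the only specific unadjusted test named for binary outcomes. At stake is the pilot's initial reading of whether incentives change testing.

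**Working it through.** **Inputs.** About 100 per arm (90 + 10, Design section), allocated 1:1. The article gives no significance level, testing rate or effect size for this comparison, so there is no stated figure to reproduce. Assumed: two-sided 5%, exactly 100 per arm, and a range of testing rates. Simulations used 200,000 replicates and McNemar's statistic (b − c)²/(b + c) without continuity correction, critical value 3.841.

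Let x and y be the numbers tested in the intervention and control arms, n = 100 each.

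**1. Applied to the arm-by-tested table.** The off-diagonal cells are b = n − x (untested, intervention) and c = y (tested, control). Then b − c = n − x − y, which has expectation zero when the two testing proportions add to 100%, not when they are equal.

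At expected counts:
- Both arms 50%: b = 50, c = 50, statistic 0.
- Both arms 60%: b = 40, c = 60, statistic 20²/100 = 4.0, already above 3.841.
- Both arms 70%: b = 30, c = 70, statistic 40²/100 = 16.
- Intervention 60%, control 40%: b = 40, c = 40, statistic 0 despite a 20-point effect.

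Hand check of the second case: with b + c near 100, rejection needs |b − c| > √(3.841 × 100) = 19.6. Here b − c has mean −20 and SD √(2 × 100 × 0.6 × 0.4) = 6.93, so the probability is about P(Z > −0.06) = 0.52.

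Simulated rejection with no true difference:

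| Tested in both arms | McNemar on the table | Pearson chi-square |
|---|---|---|
| 50% | 0.6% | 5.6% |
| 55% | 8.9% | 5.6% |
| 60% | 53% | 5.1% |
| 70% | 99.9% | 5.2% |

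With a true 60% v 40%, rejection is 1.2% for McNemar on the table and 83% for chi-square.

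**2. Applied within person over time.** Here b and c count people who changed status between two periods, so the test addresses a time trend. If testing falls from 50% to 40% equally in both arms, one arm of 100 is significant in 29% of runs (39% with within-person correlation 0.3), and both arms pooled in 52% (67%). None of that reflects the intervention.

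A special case: everyone enrolled has just had an HIV test (Characteristics of participants section). If the enrolment period is counted as tested, change can go only one way. Four later non-testers then suffice for the asymptotic test (4²/4 = 4.0) and six for the exact test (2 × 0.5⁶ = 0.031), in either arm.

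**3. Applied to arbitrary treated-control pairs.** Let a be the number of pairs with both members tested. Then b = x − a and c = y − a, so b − c = x − y, the arm difference in numbers tested, whatever the pairing. Simulated error is 4.9% to 5.1%, and power for 60% v 40% is 80.7%, against 82.5% for chi-square.

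The denominator b + c = x + y − 2a does depend on the pairing. With x = 60 and y = 40, a can be anything from 0 to 40, so b + c runs from 100 down to 20 and the statistic from 400/100 = 4.0 to 400/20 = 20. Those are the extremes. Chance pairing gives a near 100 × 0.6 × 0.4 = 24, b + c = 52 and a statistic of 7.7. The Pearson statistic for the same data is 0.2²/(0.5 × 0.5 × 2/100) = 8.0, with no pairing to choose.

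**The case against.** The strongest defence is that the plan does not depend on this test. D for a yes/no outcome is the risk difference, and logistic or logit estimation for binary outcomes is named twice. Both compare the arms properly. This stands, and it limits the point to the McNemar component.

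A reader might infer that no use of the test could address the arm contrast. The third calculation shows otherwise: with arms of equal size, arbitrary pairs do test it, with near-nominal error and power. What remains wrong is that the pairing, and hence the p-value, is invented.

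A reader might also take the 53% or 99.9% as the trial's actual error rate. The article does not say the test would be run on the arm-by-tested table, and the testing rates are assumed. Nor does it state a rule that the arms be judged by which one reaches significance over time, so error rates built on such a rule are not the plan's.

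A third inference would be that a faulty p-value decides whether a definitive trial goes ahead. No passage says so. The primary goal of the analysis is acceptability and feasibility, the one explicit threshold concerns participation, and the next trial is to be planned from point and interval estimates. The primary outcome is also described as frequency of testing, with the yes/no form only an example.

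Finally, the word linking the logistic regression to McNemar might suggest that the regression is faulty too. The text does not specify its form, and with an arm term it is a valid comparison.

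The remaining defence, that McNemar was meant only for change within person, conflicts with the purpose the sentence states.

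**Conclusion.** The sentence is wrong as written: a paired-data test is assigned to a comparison of unmatched randomised arms, against the plan's own between-group effect measure. The size of the consequence cannot be fixed, because the manner of applying the test is not stated. Under the assumptions above it ranges from nearly harmless (arbitrary pairs, about 5% error) to uninformative about the intervention (the arm-by-tested table, or change over time).

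Because valid between-arm analyses sit beside it and this is a feasibility pilot with no decision tied to this p-value, the point should be fixed but does not undermine the trial. That the test fits neither the design nor D rests on the text alone. The percentages rest on 100 per arm, a two-sided 5% level and the assumed testing rates and correlation.

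**What to change.** In the Data analysis section, replace McNemar's test with an independent-samples comparison of the proportion tested: the risk difference between arms with a 95% confidence interval, and a chi-square or Fisher's exact test if a p-value is wanted. This is D for a binary outcome. Keep logistic regression with an arm term as the covariate-adjusted version. If McNemar's test is retained, limit it to describing change over time within an arm, and say so.

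With 100 per arm the replacement test has simulated error of 5.0% to 5.6% across testing rates of 10% to 90%, and about 83% power for 30% v 50% or 40% v 60%. The cost is one sentence, with no new data and no additional participants.

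### The effect estimator is introduced on adherence and the repeated-measures analysis on sexual behaviors; neither is a listed outcome, so both labels need correcting

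*Protocol article*

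**What the plan says.** The Data analysis section of the protocol article sets out the effect analysis in three steps.

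- **Contrast.** It defines D as a simple comparison "of the group means in adherence levels", first in levels and then in changes. E[Y] itself is described only in general terms: it "indicates the expected outcome in intervention group" T and control group C. A regression of Y on treatment and covariates follows.
- **Longitudinal analysis.** The repeated-measures and time-series techniques are presented as a way to see "whether self-reported sexual behaviors persist or decline similarly between the two groups".
- **Covariates.** The ANCOVA adjusts for client characteristics that turn out to separate the groups at baseline.

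Later in the same section the article states: "With respect to the dependent variables, the primary outcomes include HIV knowledge and frequency of HIV testing; the secondary outcomes include HIV infection". The Design section gives the same primary and secondary outcomes. Table 1 lists HIV knowledge (HIV-KQ-18, at enrollment, 6 and 12 months), HIV testing behaviors from clinic data, and HIV infection. Its remaining rows are covariates.

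**The concern.** The sentence that introduces an estimator should name the variable being estimated. Here it names adherence, which the article never defines for this trial. Participants must test HIV negative to enroll, and the monitoring section says that no drugs are given, so adherence to antiretroviral treatment cannot be meant. The longitudinal sentence names sexual behaviors, for which Table 1 has no row.

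Two things are at stake. First, a reader of the public protocol cannot tell whether a later result on adherence or on sexual behaviors was prespecified. Second, the article says the pilot should supply parameters reliable enough to plan the definitive trial, and those come from contrasts on knowledge and testing. The level and change forms of D do not suit both outcomes equally, so leaving the outcome unnamed also leaves open which form applies to which.

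**Working it through.** No formula gives the mismatch itself. The check is to set the places side by side.

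| Place in the article | Outcome named |
|---|---|
| Design | Primary: HIV knowledge, testing frequency. Secondary: HIV status |
| Table 1 | Primary: HIV knowledge, HIV testing behaviors. Secondary: HIV infection |
| Data analysis, dependent variables | Primary: HIV knowledge, testing frequency. Secondary: HIV infection |
| Data analysis, sentence introducing D | Adherence levels |
| Data analysis, repeated-measures sentence | Self-reported sexual behaviors |
| Data analysis, dichotomous variables | HIV testing within a three-month period |
| Data analysis, closing summary | Retention of prevention information, as a longitudinal response |

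**Step 1: does either label match a listed outcome?** No. The first three rows agree with one another, and the fourth and fifth match none of them.

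**Step 2: could adherence be defined elsewhere?** The word otherwise appears only in Background, for antiretroviral adherence in a different study, in Uganda. It might be carried over from there. It might loosely mean keeping to the three-monthly testing target described under MOTIVES intervention. The article does not say which. On the second reading, D would cover testing but not knowledge.

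**Step 3: are the primary outcomes left without an analysis?** No. Y is generic, and the dependent-variables sentence supplies both primary outcomes. Binary testing has its own stated method in the same section. The closing summary places retention of prevention information among the longitudinal responses.

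**Step 4: which form of D fits which outcome?** Knowledge has an enrollment value, so level, change and baseline-adjusted forms are all possible. Testing frequency during follow-up has no stated pre-enrollment counterpart, because the article defines no earlier window for counting tests. The change form is therefore undefined for it as written, and the level form is the one that works.

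**Step 5: why adjust knowledge for the enrollment score?** Let the score have the same variance σ² at enrollment and follow-up, correlation ρ between the two, and n people per arm. The large-sample variances of the treatment contrast are:

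- raw difference in levels: 2σ²/n
- difference in changes: 4σ²(1 − ρ)/n
- adjusted for the enrollment score: 2σ²(1 − ρ²)/n

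The article gives no ρ, so take its whole range. Dividing by 2σ²/n gives 1, 2(1 − ρ) and 1 − ρ². The adjusted form never exceeds the raw form, because 1 − ρ² ≤ 1. It never exceeds the change form, because 2(1 − ρ) − (1 − ρ²) = (1 − ρ)² ≥ 0. This gain does not depend on whether the arms happen to differ at baseline, so making adjustment conditional on an observed difference can forgo it.

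**The case against.** The strongest reply is that the article answers the question itself. Y is defined generically, and shortly after the regression equation the text says that "the primary outcomes include HIV knowledge and frequency of HIV testing". Read together, the equation and that sentence tell an analyst what to put in for Y. The sentence on sexual behaviors says what the approach makes possible and does not restrict the model to that variable. The section also opens by making acceptability and feasibility the primary goal, so D is not the trial's main analysis.

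Most of this stands. A reader might infer from the two labels that neither primary outcome is estimated. The documents do not support that, for the reasons in Step 3. A reader might also infer that the trial targets something it does not collect. That is not established either: adherence could mean keeping to the testing schedule, and the full survey is not shown, so items on sexual behavior may exist.

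What does not stand is that nothing needs changing. The sentence introducing D does name an outcome, and it is the wrong one. Two parts of one section then disagree, and the reader has to work out which governs. This is not a matter of condensation, since the article prints the estimator and labels it incorrectly.

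**Conclusion.** The point holds as a misstated outcome in operative analysis text. Two labels in Data analysis, adherence levels and self-reported sexual behaviors, conflict with the outcomes given in Design, in Table 1 and later in Data analysis. None of the three listed outcomes is named in the sentence introducing D or in the repeated-measures sentence. No figure in the article changes.

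The consequence is limited, because the intended outcomes are recoverable and the effect comparisons come second to feasibility and acceptability. The point does not extend to requiring a single primary time point. The article plans comparisons at six-month intervals, and choosing one of them can be left to the analysis plan.

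The case for baseline adjustment rests on equal variances at the two times and on ignoring the very small cost of estimating one extra coefficient with about 100 people per arm. It does not rest on any particular correlation.

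**What to change.** In Data analysis:

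1. Where D is introduced, replace adherence levels with the HIV-KQ-18 score and HIV testing frequency.
2. For knowledge, estimate the contrast at 6 and at 12 months adjusted for the enrollment HIV-KQ-18 score, whether or not the arms differ at baseline.
3. For testing frequency during follow-up, use the level form of D.
4. Name the HIV-KQ-18 score at 0, 6 and 12 months as the repeated-measures outcome.
5. Delete self-reported sexual behaviors. If they are collected, list them in Table 1 as exploratory, with instrument and time points.

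The cost is a few sentences and at most one extra row in Table 1. Nothing new has to be collected, since Table 1 already schedules the enrollment score. The correction should be dated and made before the arms are compared on these outcomes.

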**Methods:**

The project will be conducted in collaboration with Bienestar Human Services, Inc. (*Bienestar*), a non-profit community-based service organization. The intervention is being tested in a small, randomized controlled trial to pilot the intervention’s feasibility and acceptability among 200 Latino/a MSM and TGW from *Bienestar*’s HIV testing sites. Information on feasibility will include recruitment, refusal, and retention rates as well as message sending success rates; acceptability will include perceived appropriateness based on responses to the intervention. Participants will be randomized into either the “information only” control group (e.g. receiving text messages with HIV prevention information) or the “information plus” intervention group (e.g. additionally receiving quiz questions that provide the possibility of winning prizes). Participants will be followed for 12 months from enrollment. In addition to using data abstracted from *Bienestar*’s routine data collection mechanisms, we will also collect survey data (blinded outcome assessment) from participants at 0, 6, and 12 months to provide an initial assessment of whether incentives affect their level of HIV knowledge and testing frequency.

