### Measures: health outcomes

Enrolled participants respond to a baseline assessment after they have completed screening and consent. The MOTIVES HIV tester reads the baseline survey to participants to guarantee understanding by clients across a range of literacy levels. Together the screening and consent processes take approximately 15 min to complete; the baseline survey takes approximately 30 min. Participants will complete a shortened six-month survey via response to a link sent to them on their phone. If participants cannot complete the six-month survey on their own, the Study Coordinator will offer to meet them at a local library of their choice and provide a tablet to complete the survey. However, we expect this circumstance be the exception rather than the rule. Participants will receive a $15 gift certificate via text after completing the six-month survey.

The 12-month follow-up survey will have fewer questions and will be completed after the intervention is over, Thus, completing the questions at a *Bienestar* testing location will not confound the outcome of interest. Participants will receive a $15 gift card for participating in the final survey. For those who do not complete their HIV test for that period, we will send a text message reminder to complete the final survey at *Bienestar*. Table 1 describes when each set of questions will be asked.

**Table 1 Tab1:** Health outcomes and measures of interest

Outcome	Instrument	Data collection timepoint
Primary Outcome		
HIV knowledge	Carey MP, et al. Development and psychometric evaluation of the brief HIV knowledge questionnaire (hiv-kq-18). AIDS Education and Prevention. 2002; 14: 174-184.	enrollment, 6 & 12 months
HIV testing behaviors	Extracted from *Bienestar* clinic data	
Secondary Outcomes		
HIV infection	Oraquick/Orasure	enrollment, 3, 6, 9 and 12 months
Covariates of Interest		
Socio-demographic information	Based on previous *Bienestar* questionnaire	enrollment & 12 months
Acculturation	Marín, G et al. Development of a short acculturation scale for Hispanics. Hispanic Journal of Behavioral Sciences. 1987; 9:183–205.	
Mental health	Kessler, RC et al. Short screening scales to monitor population prevalences and trends in non-specific psychological distress. Psychological Medicine. 2002; 32: 959-956.	
Substance abuse	Carballo-Diéguez, A et al. Microbicide Safety and Acceptability in Young Men: Baseline Behavioral Questionnaire. 2010.	

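### HIV infection is a secondary outcome, but no follow-up test independent of participants' choice is described, so detected infections may differ by arm; the sources given for testing frequency also need reconciling

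*Protocol article*

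**What the plan says.** **Outcomes.** The Data analysis section states that "the primary outcomes include HIV knowledge and frequency of HIV testing; the secondary outcomes include HIV infection". It adds, for binary outcomes in general, that "Logit estimation will be used for binary outcome measures". Its closing summary counts rapid-test positivity and the frequency of repeat negative tests among the parameters needed to plan the next trial.

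**Infection.** Table 1 (Measures: health outcomes) gives a rapid test as the instrument, at "enrollment, 3, 6, 9 and 12 months". The text of that section describes no HIV test given by the study at those times. The six-month contact is a survey by phone link. At 12 months the text foresees participants who have not tested in that period and sends them a reminder to complete the final survey at Bienestar.

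**Testing.** For testing behaviours, Table 1 gives the source as "Extracted from *Bienestar* clinic data". The Abstract (Methods) is wider: besides data from Bienestar's routine collection, surveys at 0, 6 and 12 months are to inform both knowledge and testing frequency.

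**Incentive.** Under MOTIVES intervention, testing at least quarterly is the target. The drawing depends on a negative test in each 12-week period and is open to half of the participants. The periodic reminder to test is described at consent, without restriction to one arm.

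**Size.** The trial is "a small RCT among 200 Latino/a MSM and TGW". The Design section adds: "There will be approximately 90 MSM and 10 TGW in each arm".

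**The concern.** Whether a participant's infection status is known after enrolment appears to depend on the behaviour that the intervention is meant to change. If one arm tests more, a larger share of its infections comes to light, and a comparison of positives then mixes incidence with ascertainment. The planned imputation and dropout weights do not obviously help: they address missing variables and dropout, not people who stay enrolled but do not test.

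The second issue concerns a primary outcome. If testing frequency is scored from Bienestar records alone, a participant who moves a test from another provider to Bienestar counts as testing more when total testing is unchanged.

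Both quantities are meant to feed the design of the definitive trial, so a distorted arm contrast would be carried forward.

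**Working it through.** The protocol states no incidence, re-testing rate or share of outside testing, so it has no figure to reproduce. From the document: 90 + 10 = 100 per arm, 2 × 100 = 200 in total, 12 months of follow-up and a quarterly testing target. All other inputs below are assumptions.

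**1. Detected infections, simple case.** Detected proportion = true incidence × proportion ever re-tested.

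- Intervention: 3% × 0.85 = 2.55 per 100.
- Control: 3% × 0.60 = 1.80 per 100.
- Ratio: 2.55 / 1.80 = 1.42, with no true difference. The gap is 0.75 of a person per 100.
- With 80% versus 60% re-tested, the ratio is 2.40 / 1.80 = 1.33.

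**2. Detected infections, quarterly testing.** Let each participant test at the end of each quarter with probability q, independently. An infection counts if any later test occurs. With infections spread almost evenly over the year, the share found is about the average of 1 − (1 − q)^k for k = 1 to 4.

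| q, control vs intervention | Share found | Ratio |
|---|---|---|
| 0.25 vs 0.40 | 49% vs 67% | 1.38 |
| 0.25 vs 0.50 | 49% vs 77% | 1.57 |
| 0.40 vs 0.60 | 67% vs 84% | 1.24 |
| 0.50 vs 0.50 | 77% vs 77% | 1.00 |

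The ratios are the same at 1%, 2% and 5% annual incidence. The last row shows that the bias vanishes when testing is equal.

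**3. Can the odds ratio be estimated?** P(no detected infection in an arm of 100) = (1 − p)^100.

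- At 2.55%: 0.9745^100 = 0.076. At 1.80%: 0.982^100 = 0.163.
- At least one arm with none: 1 − (1 − 0.076)(1 − 0.163) = 0.23.
- With the same detected proportion in both arms, the figure is 60%, 25% and 9% at 1%, 2% and 3%.
- For the separate analysis of transgender women, about 10 per arm, at 3%: 1 − (1 − 0.97^10)² = 0.93.

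**4. Shift of test site.** If 10% of intervention participants move one outside test a year to Bienestar, the recorded mean rises by 0.10 × 1 = 0.10 tests, or 2.5 percentage points per quarter. The chance of a significant result is approximately Φ((|p₁ − p₂| − 1.96·se₀)/se₁), where se₀ is pooled and se₁ unpooled, plus the small opposite tail.

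- Mild shift, 30% vs 32.5% recorded: 0.057 + 0.010 = about 7%, against a nominal 5%.
- Half of each arm testing somewhere in a quarter, Bienestar share 50% vs 70%: recorded 25% vs 35%, about 34%.
- The same with shares of 60% vs 90%: recorded 30% vs 45%, se₀ = 0.0685, se₁ = 0.0676, (0.15 − 0.134)/0.0676 = 0.23, about 59%.

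The result depends almost wholly on how much testing happens elsewhere.

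**The case against.** **Infection.** Table 1 does list fixed time points, so the absence of a test independent of choice is an inference from what the text describes. The reminders to test are not described as limited to one arm. Both arms are invited to complete the 12-month survey at a Bienestar testing location for a gift card, and infection persists, so a test around that visit would pick up earlier infections in either arm. This could narrow the gap, but nothing described ensures a test at that visit, and the text expects some to be missed.

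**Direction.** A reader might infer that infections are bound to be detected unequally, or that an effective intervention must appear to raise infection. The document does not support either. The bias requires a change in testing, and a prize conditional on a negative result could deter those who suspect infection.

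**Logit.** The sentence on logit is generic and does not name infection, and the protocol also intends point and interval estimates of key parameters. A reader might infer that the model would usually fail. In the main illustration the chance of an empty cell is about 23%, and it is 60% only at 1% detected incidence.

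**Testing frequency.** A reader might take Table 1 to mean that testing is observed only at Bienestar. The Abstract names surveys as a further source. Their items are not shown, so one on outside tests may already exist. Nor does the protocol say that a test must be at Bienestar to count for the drawing.

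**Weight.** This is a feasibility pilot, and infection is secondary. That limits the point but does not remove it, because the affected quantities are among those intended for planning the next trial.

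**Conclusion.** The point on infection holds in conditional form. As described, ascertainment depends on participants choosing to test, testing is rewarded in one arm only, and no correction for unequal testing among those still enrolled is given. If the intervention changes testing, a between-arm comparison of infection does not isolate incidence. Under the assumed inputs the spurious ratio runs from 1.24 to 1.57, with 1.42 in the main illustration. In absolute terms that illustration is less than one infection per 100. More detection in the intervention arm is likely, not assured.

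On testing frequency the finding is narrower: Table 1 and the Abstract give different sources, and under the record-only reading a shift of site could be counted as an increase. Its size cannot be judged from the document; the assumed scenarios range from trivial to serious.

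**What to change.** 1. **Infection.** Report it descriptively by arm: positives, persons ever re-tested, tests done, and exact confidence intervals. For scale, 2 of 100 has an exact 95% interval of 0.2% to 7.0%. State that status is unknown for those not tested, and exclude this outcome from the between-arm logit.
2. **Testing frequency.** Reconcile Table 1 with the Abstract. Label the record-based primary outcome as testing at Bienestar. Using the 6- and 12-month surveys, analyse total tests at any site as a pre-stated sensitivity analysis. If the surveys lack an item on the number and dates of tests elsewhere, add one.

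The cost is some wording and at most one survey item. The downsides are that the survey count is self-reported and that infection loses its formal comparison.
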